### Recruitment {15}

Recruitment is carried out from patients of the participating hospitals who present electively or via the emergency room and are planned to have an endovascular procedure and meet all inclusion criteria. Currently each participating hospital performs approximately 200 endovascular procedures annually in the OR. With an estimated participation rate of 25% of the eligible patients, the calculated number of 160 patients should be reached in 10–12 months.

## Assignment of interventions: allocation

### Sequence generation {16a}

Once baseline assessments and patient enrollment are completed, participants will be randomized in a 1:1 ratio using a simple envelope randomization. No dedicated sequence generation is used in this study. The envelopes were prepared by the study office staff and are kept in a container by them following thorough mixing. The envelopes are outwardly identical. The surgeons participating in the study are not involved in the randomization process. Participants will draw their envelope out of a pool of the remaining allocations after enrollment.

### Concealment mechanism and implementation {16b} {16c}

Allocation concealment for all participants is ensured by using sequentially numbered opaque envelopes. All envelopes are prepared at the beginning of the study by a study nurse not involved in the inclusion and randomization of the patients.

Patients will be enrolled to the study by their treating physician and randomization will be performed post-consent. Participants will be randomized to Vascular Navigation PAD group or standard imaging techniques in a ratio of 1:1 post-consent and confirmation of eligibility.

## Assignment of interventions: blinding

### Blinding {17a}

Due to the nature of the intervention, it is not possible to blind the surgeon and outcome assessor. After randomization, the study team is aware of the allocation.

Emergency unblinding is not required in this study.

The data statisticians will be blinded to treatment allocation. The datasets from the two groups are handed over to the statisticians in a blinded manner for primary statistical analysis.

### Procedure for unblinding if needed {17b}

N/a; there will be no blinding in this trial.

## Data collection and management

### Data collection methods {18a}

Sites will be provided with a paper-based case report form (CRF) containing the relevant data required to be collected. Outcomes are noted by the operation team or the surgeon.

### Plans to promote participant retention and complete follow-up {18b}

No plans to promote participant retention and complete follow-up are established, as participation ends after the hospital index stay.

### Data management {19}

All study data will be handled confidentially by the investigational team and recorded using a case report form (CRF). The patient data reported in the CRFs shall be derived from source documents, be consistent with these, and any discrepancies shall be explained in writing.

### Confidentiality {27}

Any personal data will only be seen by the treating physicians and necessary hospital staff and will remain at the hospital. All data will be pseudonymized and a subject ID log will be securely stored at the hospital in a database locally in the secure hospital network before transferring to Brainlab. Only the hospital’s trained study staff has access to this information. Under no circumstances shall Brainlab have access to the subject ID log. All subjects shall consent to the processing (including the anonymization of their data by Brainlab) and transfer of their pseudonymized data to Brainlab AG and its subsidiaries.

The CRFs will be stored until at least 15 years in Brainlab’s content management system, Windchill, with restricted access until after the last Vascular Navigation PAD has been on the market. Data in Windchill will be handled according to Brainlab’s technical and organizational measures.

### Plans for collection, laboratory evaluation, and storage of biological specimens for genetic or molecular analysis in this trial/future use {33}

N/a; there will be no collection of biological specimens.

## Statistical methods

### Statistical methods for primary and secondary outcomes {20a}

The primary and secondary endpoints will be summarized as mean ± standard deviation or median, as appropriate. Because contrast agent volume and radiation dose are continuous variables and each participant contributes one observation, group comparisons will be performed using an unpaired two-sample *t*-test if the data are approximately normally distributed. The primary analysis will be conducted according to the intention-to-treat principle.

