**Methods:**

This is a multicenter, prospective, randomized confirmatory trial comparing navigation-assisted procedures with conventional procedures without navigation assistance. Patients allocated to the intervention group will undergo treatment using Vascular Navigation PAD in addition to a mobile C-arm. A total of 160 patients will be randomized in a 1:1 ratio, with 40 patients per group enrolled at each of the two participating hospitals. The primary endpoint is contrast agent volume. Secondary endpoints include patient radiation exposure, physician radiation exposure, fluoroscopy time, and the number of DSAs performed per intervention.

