#### Performing surgeons

The interventions will be performed by a specialist in vascular surgery at the two participating hospitals.

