#### Secondary outcome

The secondary endpoints are:Radiation dose received by patients, quantified in the dose-area product (DAP) (µGy·cm^2^) and cumulative air kerma (Gy)Radiation dose received by the physicians, quantified in microsievert (µSv) measured with a personal dosimeter worn at the chest above the lead apron vestQualitative assessment of the device ability to enable navigation of endovascular devices to defined targets in PAD procedures using a 5-point Likert scale

All data shall be recorded by the OR team at the time of the procedure immediately after the sheath is removed.

In addition, the influence on the procedural time in minutes, number of DSAs, fluoroscopy time in minutes, and consumables per lesion shall be noted.

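### The one-observation-per-participant rationale for the t-test does not cover physician radiation dose; the likely cost is some precision, not a raised error rate

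*Protocol article*

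**What the plan says.** Section {20a} of the protocol article covers primary and secondary outcomes together. It gives one test, an unpaired t-test provided the data are approximately normal, with one reason: "contrast agent volume and radiation dose are continuous variables and each participant contributes one observation". It does not say whether radiation dose means the patient's, the physician's or both.

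The Secondary outcome section lists both. Patient dose is dose-area product and cumulative air kerma. Physician dose is in microsievert, from a personal dosimeter that the physician wears over the lead apron. On timing it says: "All data shall be recorded by the OR team at the time of the procedure immediately after the sheath is removed". The secondary objectives list physician dose as an item of its own.

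On who operates, Performing surgeons says: "The interventions will be performed by a specialist in vascular surgery at the two participating hospitals". No number is given, but the Survey data section averages ratings over all surgeons, so there is more than one. On volume, the abstract says: "A total of 160 patients will be randomized in a 1:1 ratio, with 40 patients per group enrolled at each of the two participating hospitals". On allocation, {16a} says that "participants will be randomized in a 1:1 ratio using a simple envelope randomization" and that "The surgeons participating in the study are not involved in the randomization process". The analysis sections mention no physician term.

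**The concern.** For contrast volume, dose-area product and air kerma, the person measured is the randomized patient, and one value per patient is a fair description. For physician dose, the person measured is the operator. The same operator wears the dosimeter in case after case, normally in both arms, and habits such as standing position and use of shielding would make that operator's readings alike. Counting one record per participant does not address this likeness.

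Physician exposure is a named secondary objective and part of the device's case in the abstract and discussion. If operators differ materially, a test that leaves those differences in the error term has less power than it could have. The operator's identity must also be recorded for each reading; on paper CRFs it may be hard to recover later.

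**Working it through.** **The plan's own figure.** None exists for physician dose. The sample-size section concerns contrast volume only, so there is nothing to reproduce.

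**Are repeated readings certain?** There are 160 procedures (about 160 × 0.9 = 144 after the plan's 10% dropout), two hospitals and one record per procedure. With an assumed 4 to 8 physicians, that is 144/8 = 18 to 144/4 = 36 readings each. The number of physicians is not in the document, but one physician per patient is not plausible.

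**Assumptions.** N = 144, 72 per arm; total SD 1; effect 0.45 SD; two-sided 5%; K = 4 or 8 physicians with equal caseloads; ICC (share of variance between physicians) 0 to 0.4; the same device effect for every physician.

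**Type I error.** Under patient-level randomization, a physician's level is shared by that physician's cases in both arms and does not favour either arm on average. Two sets of simulations agree:

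- 160 procedures, 2 or 5 physicians per site, ICC 0-0.3: t-test error 4.3-5.1% with arms balanced within site, 5.0-5.4% without.
- 144 procedures, 4 or 8 physicians, ICC 0-0.4: 4.6-5.6%.

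Repeated readings alone therefore do not inflate the test.

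**Power, by approximation.**

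- Unpaired t-test: 0.45 × √(144/4) = 0.45 × 6 = 2.70; power ≈ Φ(2.70 − 1.96) = Φ(0.74) = 0.77.
- Physician as a factor: the residual SD falls to √(1 − ICC), and chance imbalance within physicians keeps a fraction f = 1 − (K − 1)/(N − 1) of the information. That is 140/143 = 0.979 for K = 4 and 136/143 = 0.951 for K = 8. The signal is 2.70 × √f / √(1 − ICC).

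| ICC | K = 4: signal, power | K = 8: signal, power |
|---|---|---|
| 0 | 2.67, 0.76 | 2.63, 0.75 |
| 0.1 | 2.82, 0.80 | 2.78, 0.79 |
| 0.4 | 3.45, 0.93 | 3.40, 0.92 |

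**Power, by simulation.** At ICC 0.1-0.4 the t-test had about 77-81% and the physician model 78-93%, a gain of about 1 to 14 points. At ICC 0 the physician model lost 1-2 points. The simulated t-test does slightly better than 0.77 at high ICC because the realised spread among a handful of physicians is on average below its population value. With 160 procedures and 2 physicians per site, the pairs were 0.81 against 0.83 (ICC 0.1) and 0.85 against 0.92 (ICC 0.3).

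**When would error exceed 5%?** Two conditions do it, and the document states neither.

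1. *Device cases concentrated on certain operators.* If every physician's split is fixed at 60/40, simulated t-test error is 7-12%; at 70/30 it is 12-29% (ICC 0.2-0.4). Randomization makes such splits very unlikely. With 36 cases each, the chance that one physician departs by at least 60/40 in either direction is 0.243, and for all four 0.243⁴ ≈ 0.003. For 70/30 it is 0.0113⁴ ≈ 1.6 × 10⁻⁸.
2. *A device effect that differs between physicians.* With effect variance 0.02-0.10 and ICC 0.1, t-test error was 7-16% with 2 physicians per site and 5-9% with 5. Physician intercepts did not cure this: 8-17% and 6-10%.

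**The case against.** The unit of randomization and of record is the procedure, and each procedure yields one physician-dose entry. Read that way, the sentence in {20a} is loose rather than false. It also says only radiation dose, and its t-test is conditional on normality. Under randomization, leaving out a prognostic factor is not an error, and choosing covariates is ordinarily work for the analysis plan. Operators influence contrast volume and patient dose too, so physician dose is not uniquely affected. No power is claimed for this endpoint.

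Most of this stands, and it is why the point is minor. It does not remove the point, because the article goes beyond leaving the model open. It gives a reason for independence in a section covering all secondary outcomes, and that reason does not reach an endpoint measured on the operator.

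A reader might go further and infer that the t-test will give too many false positives for physician dose. The document does not support that. Patients are drawn individually 1:1, surgeons take no part in the draw, and nothing assigns operators by arm. It is true that the allocation is known before the procedure ({11c}, {17a}) and that no rule fixes the operator before the envelope is drawn. That leaves such selection possible but does not describe it. A reader might also take the plural physicians to mean several dosimeter readings per procedure; it fits different operators across procedures equally well.

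**Conclusion.** The point holds in limited form. One observation per participant does not establish independence for physician dose, because that endpoint is measured on operators who will almost certainly contribute repeatedly. The expected cost is precision: about 1 to 14 points of power at a 0.45 SD effect for ICC 0.1-0.4 and 4-8 physicians, and none at ICC 0. The ICC, the number of physicians and the effect size are all assumptions, since the document gives none of them. Error stays near 5% unless operators are chosen after allocation or the device effect differs between physicians. The primary endpoint's test is not called into question here. Minor: a cheap improvement on a named secondary endpoint.

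**What to change.** In {20a}, limit the one-observation rationale to endpoints measured on the patient. For physician dose, state that one reading per procedure, from the main operator, will be analysed in a linear model of dose on arm with physician as a factor. Add a pseudonymous operator code to the CRF for each reading, and start now, since recruitment is under way.

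The cost is one analysis sentence, one CRF field and a few degrees of freedom (1-2 points of power if physicians do not in fact differ). No extra patients or procedures are needed. The model assumes a common device effect across physicians. It does not protect against an effect that varies between them, and the text should say so.

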**Table Tabb:** 

Timepoint	*t* < 0	Enrollment		Post-intervention/discharge
		0	1	2 (end of intervention)
Enrollment				
Eligibility screen	X			
Informed consent	X			
Randomization		X		
Intervention (operation with or without Vascular Navigation PAD)			X	
Assessments				
Baseline characteristics (age, weight, height)	X			
Renal function	X			
Pre-existing condition (diabetes, coronary heart disease)	X			
Contrast agent used				X
Fluoroscopy time				X
Air kerma				X
Dose-area product				X
Procedural time				X
Number of angiography series				X

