### Sample size {14}

It is the aim of this study to determine the investigational device’s ability to reduce the nephrotoxic contrast agent volume required during endovascular procedures of the lower extremities. Existing clinical literature suggests a potential reduction of 30% in the volume of contrast agent when comparing procedures with navigation support to those without it [7, 9]. Additionally, information on usually needed contrast agent during procedures without navigation support is provided by a systematic review [9]. Reported values are as follows:Navigation-supported group = 34.7 ± 13.8 mLNon-navigated group (control):◦ Group 1 = 51.3 ± 26.7 mL [7])◦ Group 2 = 88.31 ± 55.35 mL (systematic review, [10])◦ Group 3 = 81.14 ± 58.68 mL (systematic review, [10])

Based on this clinical literature, the expected mean contrast volume was assumed to be 88.16 mL in the control group and 34.7 mL in the navigation-assisted group, corresponding to an anticipated absolute reduction of 53.46 mL. For sample size planning, a superiority margin of 30% of the control-group mean was prespecified, corresponding to 26.45 mL, which was used as the clinical threshold for superiority and not as the expected treatment effect. Assuming a common standard deviation of 55.27 mL, a two-sided significance level of 0.05, and a power of 90%, the required sample size was calculated for a two-group superiority design with a continuous endpoint.

After allowing for a dropout rate of 10%, 80 patients per group were planned.

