### Methods for additional analyses (e.g., subgroup analyses) {20b}

A subgroup analysis will be executed on all endpoints based on indication/diagnosis, lesion location, and amount and type of endovascular devices used and placed (e.g., stents).

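### The secondary radiation endpoints are compared without adjustment for baseline weight and height, which gives up a modest amount of precision at no saving

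*Protocol article*

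**What the plan says.** Statistical methods {20a} gives one rule for contrast volume and radiation together. The reason stated is that "contrast agent volume and radiation dose are continuous variables and each participant contributes one observation", and the consequence is that "group comparisons will be performed using an unpaired two-sample *t*-test if the data are approximately normally distributed". No covariate is named, and no alternative is given if the data are not roughly normal.

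Secondary outcome, under Outcomes {12}, defines the radiation endpoints. For the patient they are dose-area product (DAP) and cumulative air kerma. For the operator the endpoint is "Radiation dose received by the physicians, quantified in microsievert (µSv) measured with a personal dosimeter" worn at the chest.

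The schedule table under Participation timeline {13} places weight and height in the column before enrolment (the row begins "Baseline characteristics (age, weight, height"). Sequence generation {16a} confirms that baseline assessments are complete before the envelope is drawn.

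The only further analysis described, in section {20b}, is by subgroup: "A subgroup analysis will be executed on all endpoints based on indication/diagnosis, lesion location, and amount and type of endovascular devices used". Body size is used nowhere.

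**The concern.** X-ray output can be expected to rise with the thickness of the body part imaged, and the inclusion criteria admit iliac as well as leg disease. Part of the spread in DAP and air kerma between patients may therefore reflect body size and not the device. An unadjusted two-sample test leaves that part in the error term. The documents do not quantify this link, so it is treated here as an assumption.

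Lower radiation exposure is a leading secondary aim in the Abstract, the Secondary objectives and the Discussion. Sample size {14} rests on contrast volume alone and gives no SD, effect or power for any radiation endpoint. Precision for radiation is thus whatever 80 patients per group and the chosen analysis provide. The covariates that could improve it are already being collected.

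**Working it through.** **Plan's own figure.** There is none to reproduce for radiation. The planned 80 per group is taken as given. Whether the stated inputs lead to 80 is a separate question about the primary endpoint and does not enter here.

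**Inputs from the documents.** 80 per group with 10% dropout leaves 80 × 0.9 = 72 evaluable per arm. The two-sided 0.05 level is borrowed from Sample size {14}, which states it for the primary endpoint.

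**Assumptions (not in the documents).** Log-scale SD of dose 0.9 (range 0.7 to 1.1); true reduction 30%, so the log effect is |ln 0.7| = 0.357; weight SD 15 kg; dose change 1%, 2% or 3% per kg.

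**Step 1: unadjusted precision.** SE = 0.9 × √(2/72) = 0.150. The noncentrality is 0.357/0.150 = 2.38, and noncentral-t power is 66%. It is 86% at SD 0.7 and 49% at SD 1.1.

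**Step 2: share of variance explained by weight.** R² = (change per kg × 15 / SD)². The adjusted SE is SD × √(1 − R²) × √(2/72). The equivalent unadjusted size is 72/(1 − R²). At SD 0.9:

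| Dose change per kg | R² | Correlation | SE | Power | Equivalent unadjusted n per arm |
|---|---|---|---|---|---|
| none (unadjusted) | 0 | 0 | 0.150 | 66% | 72 |
| 1% | 0.028 | 0.17 | 0.148 | 67% | 74 |
| 2% | 0.111 | 0.33 | 0.141 | 71% | 81 |
| 3% | 0.250 | 0.50 | 0.130 | 78% | 96 |

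Over the same 1–3% range, power goes from 86% to 87–98% at SD 0.7 (R² 0.05 to 0.41) and from 49% to 50–56% at SD 1.1 (R² 0.02 to 0.17). Height may add to R² by an amount that cannot be set from the documents.

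**Step 3: the same question without a log SD.** Take an effect for which the unadjusted test has 80% power at 72 per arm (0.467 SD). Replacing the SD by SD × √(1 − ρ²), where ρ is the correlation of dose with body size, gives:

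| ρ | Adjusted power |
|---|---|
| 0.1 | 80.4% |
| 0.2 | 81.6% |
| 0.3 | 83.6% |
| 0.4 | 86.4% |
| 0.5 | 89.9% |

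A simulation with two covariates (8,000 runs per value of ρ) gave t-test against adjusted power of 78.9% and 82.5% at ρ = 0.3, and 80.1% and 89.6% at ρ = 0.5.

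**Step 4: cost if body size does not matter.** Two covariates reduce the residual degrees of freedom from 142 to 140, so the SE grows by √(142/140) = 1.007, or 0.7%. The simulation at ρ = 0 gave 79.8% unadjusted and 79.4% adjusted.

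**Step 5: is chance imbalance a further problem?** With 72 per arm, the SE of the difference in mean weight is 15 × √(2/72) = 2.5 kg. At 3% per kg this contributes 2.5 × 0.03 = 0.075 to the log ratio. Adding it to the adjusted SE in quadrature gives √(0.075² + 0.130²) = 0.150, which is the unadjusted SE of Step 1. The unadjusted interval therefore already allows for it.

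**The case against.** The strongest reply is that covariates for secondary endpoints usually belong in the statistical analysis plan, that a journal article condenses the full protocol, and that nothing here is wrong. In a randomised trial the unadjusted comparison is unbiased and keeps its type I error. This largely stands and fixes the severity. It does not remove the point, because the article does not leave the method open. It names a test for radiation dose, and a better one is available from data already collected. A separate plan may add adjusted models, but the text as published does not point to any.

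Three stronger readings are tempting and are not supported.

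- A reader might infer that chance imbalance in weight would bias the radiation result, or that the envelope draw makes this worse. Step 5 shows that the unadjusted standard error already covers such imbalance, and no allocation scheme balances body size unless it stratifies on it.
- A reader might infer a large gain, for example 86% power if body size explained 40% of log-dose variance. At SD 0.9 and a weight SD of 15 kg, that needs 0.9 × √0.40 / 15 = 3.8% per kg from weight alone, which is outside the assumed range.
- A reader might apply the same gain to all three endpoints. Physician dose is read from a chest dosimeter, and its link to patient size may be weaker.

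It is also fair to say that the t-test is conditional on approximate normality, so the article does not impose it on skewed dose data. It simply names nothing for that case.

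**Conclusion.** The point holds as a minor one. The stated analysis of DAP, cumulative air kerma and physician dose is valid but less precise than the baseline data allow.

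Under the assumptions listed, with SD 0.9, adjustment raises power from 66% to 67–78%, a gain of about 1 to 12 percentage points. Across the SD range of 0.7 to 1.1 the gain also lies within about 1 to 12 points. It is negligible at a correlation of 0.2 or less and becomes material from about 0.4. These sizes rest wholly on assumed values for the dose SD, the effect and the link with weight, because the documents give none. The gain is least certain for physician dose. The conclusion concerns efficiency on secondary endpoints only. It does not bear on bias, on type I error or on the primary analysis.

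**What to change.** In Statistical methods {20a}, separate the radiation endpoints from contrast volume. For DAP and cumulative air kerma, prespecify a linear model with treatment and baseline weight and height (or BMI), fitted on the log scale if dose is skewed. Apply the same model to physician dose, noting that the gain there is less certain. Report the adjusted ratio of geometric means (or the adjusted mean difference if no log scale is used) with a 95% confidence interval, and keep the unadjusted comparison as a sensitivity analysis.

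This takes a sentence or two of analysis text and needs no new data, visits or patients. The statistical cost is about 0.7% in standard error if neither covariate is prognostic. On the log scale the effect is read as a ratio and not as a difference in dose units. Trial status gives October 2026 as the planned end of recruitment. The model should be fixed before the radiation data are analysed, since an adjustment added afterwards would look post hoc.

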#### Primary objective

The primary objective is to determine the ability of the Vascular Navigation PAD to reduce the volume of administered contrast agent compared to procedures performed without the device.

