### Trial design {8}

This study is a multicenter, two-arm, prospective, confirmatory randomized superiority trial comparing a study group (navigation assistance) with a control group (procedure without navigation assistance). Patients with a clinical diagnosis of PAD who are eligible for endovascular treatment will be randomized to standard treatment or treatment with the Vascular Navigation PAD system in a 1:1 ratio.

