### Outcomes {12}

#### Primary outcome

Primary efficacy parameter of the study is the final value administered contrast agent volume of a manufacturer iodine (concentration of 300 µg/mL) at the end of the procedure. The value is measured by the local research team.

The mean volume will be compared between the intervention and the control group.

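### The 26.45 mL superiority margin that sizes the trial is not carried into the primary analysis, which names only an unpaired t-test

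*Protocol article*

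**What the plan says.** All places are in the protocol article.

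- **Trial design {8}** calls the study a "multicenter, two-arm, prospective, confirmatory randomized superiority trial comparing a study group" with navigation to a control group without it.
- **Primary objective** states the aim as follows: "determine the ability of the Vascular Navigation PAD to reduce the volume of administered contrast agent compared to procedures performed without the device". No minimum reduction is named.
- **Primary outcome** under Outcomes {12}: "The mean volume will be compared between the intervention and the control group". Again no margin.
- **Sample size {14}** assumes means of "88.16 mL in the control group and 34.7 mL in the navigation-assisted group" and describes them as "corresponding to an anticipated absolute reduction of 53.46 mL". It then sets a margin of 30% of the control mean, 26.45 mL, "which was used as the clinical threshold for superiority and not as the expected treatment effect". The other inputs are a common SD of 55.27 mL, two-sided alpha 0.05, 90% power and 10% dropout, giving 80 per group.
- **Statistical methods {20a}** says that "group comparisons will be performed using an unpaired two-sample" t-test, conditional on approximate normality and under intention to treat. It states no null hypothesis, margin or success rule.

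**The concern.** A superiority margin defines what the trial must show. If 26.45 mL is the threshold, the null hypothesis is that the mean reduction is 26.45 mL or less, and the data must exclude that. An unpaired t-test given without further qualification is normally read as a test of equal means, and the objective and outcome sections point the same way.

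These are different questions with different answers over a wide range of results. A moderate reduction could be clearly different from zero and still be compatible with a true reduction well below the threshold. For a confirmatory trial, whether superiority was shown would then depend on which section the reader takes as governing. The surgeon and the outcome assessor are unblinded, so the rule should be settled before results are known.

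**Working it through.** **Inputs, all from Sample size {14}.** Expected reduction 88.16 − 34.7 = 53.46 mL. Margin 0.30 × 88.16 = 26.45 mL. Distance from expected effect to margin 53.46 − 26.45 = 27.01 mL. SD 55.27 mL in both groups. Power 90%. Dropout 10%.

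**Step 1: which test does 80 per group come from?** Normal approximation: n per group = 2 × SD² × (z_alpha + z_power)² / Δ², then divide by 0.9 and round up. With 2 × 55.27² = 6109.5:

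| Null and Δ | Sidedness at 0.05 | Evaluable per group | Randomized per group |
|---|---|---|---|
| Margin null, Δ = 27.01 | one-sided | 72 | **80** |
| Margin null, Δ = 27.01 | two-sided | 88 | 98 |
| Zero null, Δ = 53.46 | two-sided | 23 | 26 |
| Zero null, Δ = 53.46 | one-sided | 19 | 22 |
| Zero null, Δ = 26.45 | two-sided | 92 | 103 |
| Zero null, Δ = 26.45 | one-sided | 75 | 84 |

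First row worked out: 6109.5 × (1.645 + 1.282)² / 27.01² = 71.7, rounded up to 72, and 72 / 0.9 = 80. Only the margin-shifted null gives 80, and only at one-sided 0.05, although the section states two-sided 0.05.

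**Step 2: what must be observed under each rule?** With 80 × 0.9 = 72 evaluable per group, SE = 55.27 × √(2/72) = 9.21 mL and t(0.975, 142 df) = 1.977.

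- Zero null, two-sided 0.05: 1.977 × 9.21 = 18.2 mL.
- Margin null, two-sided 0.05: 26.45 + 18.2 = 44.7 mL.
- Margin null, one-sided 0.05: about 41.7 mL.

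With all 80 per group evaluable (SE 8.74 mL), the two-sided limits are 17.3 and 43.7 mL.

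**Step 3: how often would the rules disagree?** The probability that the observed reduction lies between the two limits (72 per group, two-sided 0.05, normal approximation, with limits 18.1 and 44.5 mL):

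| True reduction (mL) | Beats zero | Beats margin | Beats zero only |
|---|---|---|---|
| 26.45 | 81.9% | 2.5% | 79% |
| 30 | 90.3% | 5.8% | 84% |
| 40 | 99.1% | 31.2% | 68% |
| 53.46 | >99.9% | 83.5% | 17% |

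**Step 4: power of the margin rule.** At a true 53.46 mL and two-sided 0.05: 27.01 / 9.21 = 2.93, and Φ(2.93 − 1.96) = 83.5% (83.0% with the t distribution). With 80 evaluable it is about 87%. At one-sided 0.05 and 72 evaluable it is 90.1%.

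**The case against.** The strongest reply is that Statistical methods {20a} names a family of tests and does not print a null hypothesis. A t-test can be run against 26.45 mL, and the only written threshold for superiority is the one in the Sample size section. The two sections could therefore be read together as a shifted-null test, with the formal hypothesis left to an analysis plan that is not shown. This stands in part. A reader might infer that the protocol prescribes a test of zero difference, or that it lays down two explicit rules so that one result formally counts as success and failure. The text does not go that far: the zero null is the default reading, supported by the objective and outcome sections, and it is not a stated rule.

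A second reply is that the margin was only for planning, since it is introduced in that context. The same sentence calls it the threshold for superiority, and the sample size depends on it. If it has no role in the decision, the rationale for 80 per group fails.

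Third, the size of the gap depends on assumptions. The navigation-group SD quoted from the literature is 13.8 mL. With that and 55.27 mL for control, SE = √((55.27² + 13.8²)/72) = 6.71 mL, the band becomes about 13 to 40 mL, and disagreement at 53.46 mL falls to about 2%. Disagreement is common only if the true effect is well below plan. That 26.45 mL itself lies inside the band adds nothing, since any margin above 18.2 mL would.

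Finally, a reader might infer that the rule can freely be chosen after the result is seen. The statisticians receive blinded datasets for the primary analysis and no interim analysis is planned. This lowers the risk but does not remove it, because the text still does not say which rule governs.

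**Conclusion.** The point holds as an inconsistency in the success criterion, not merely as missing detail. The Sample size section fixes 26.45 mL as the superiority threshold and its 80 per group follows only from a null shifted to that margin, while the objective, outcome and analysis sections never carry the margin forward. On the default zero null, observed reductions of about 18 to 45 mL (about 42 mL if the margin test is one-sided) would be called superior without meeting the prespecified threshold. The chance of this is about 79% at a true reduction of 26.45 mL and 17% at the planned 53.46 mL.

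These figures assume 72 evaluable per group and a common SD of 55.27 mL. An unseen analysis plan may state the shifted null. The published text would still need to agree with it.

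**What to change.** Before database lock, state one null hypothesis and one success rule for the primary endpoint, identically in Sample size {14} and Statistical methods {20a}.

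- **Consistent with the margin as now described:** claim superiority only if the lower limit of the two-sided 95% CI for mean(control) minus mean(navigation) exceeds a fixed 26.45 mL. Say that it is fixed, because 30% of the observed control mean would be a different threshold if that mean is not 88.16 mL. A lower limit above 0 but not above 26.45 mL is reported as a reduction that did not meet the prespecified threshold.
- **If a zero-difference test is intended:** the Sample size section must stop calling the margin the threshold for superiority and give a new rationale for the sample size. At two-sided 0.05, that test needs only 23 evaluable per group for 90% power at 53.46 mL. With 72 it has about 82% power at a true reduction of 26.45 mL.

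In either case, restate sidedness and power to match. The margin rule at two-sided 0.05 has about 83% power with 72 evaluable per group. Reaching 90% takes 88 evaluable (98 randomized) per group, or one-sided 0.05 with the present size.

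The cost is a few sentences in two sections and no new data. Under the margin rule, the superiority claim becomes harder to make and the stated power less favourable.
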